### Assignment of interventions (randomisation)

Sequence generation will be done via a computer, automated, centralised, randomisation program hosted by the Griffith Randomisation Service. The participants will be in randomised in permutated blocks of sizes two and four so the primary investigator cannot predict the allocation sequence. The participants will be stratified based on whether they are a hand vs foot burn or whether they are being debrided in theatre vs ED. Both recruitment and randomisation will be done by the primary investigator. Once the investigator has consented the patient, they will log onto the service, enter the stratification details and a participant ID and then the group allocation will be generated.

### Blinding

Due to the nature of the study, double blinding will not be possible as both the treating clinicians and the participant will be aware of the treatment modality. Even if NPWT were to be applied to all participants but blinded to whether the intervention has been turned on, it is evident when looking at the dressing what treatment group the participant is in. It will be possible however to blind the clinicians to some of the secondary outcomes. Time to re-epithelialisation will be calculated based on when a blinded panel of clinicians deem photographs of the wound to be 95% re-epithelialised. Similarly, scar thickness will be measured based on three blinded ultrasound photographs. In addition, to minimise bias based on observation of wound re-epithelialisation, any surveys or questions regarding the patient’s progression will be asked of staff/patients before the dressings are removed.

### Ancillary and post-trial care

Standard post-acute care including routine, multi-disciplinary PLCBC scar follow-up will be done.

### Outcomes

#### Pilot trial primary outcomes

Previous acute paediatric burn RCTs have shown that theoretical frameworks for feasibility are often unachievable [27, 29–32]. Given the specificity of the type of burn (significant hand and/or foot burns), it is likely that eligible participants will form a small subcohort. In addition, dropout rates may be higher for the 3-month follow-up especially if there is no scar and the only reason to attend the appointment is for research purposes. Therefore, for this study, a modified feasibility framework has been developed based on the guidelines of Polit and Beck [33] (Table 2). If at the completion of this trial the results are inconclusive or have raised further questions, this study will help guide the feasibility parameters of a larger study.

**Table 2 Tab2:** Study feasibility parameters

Nil minimum screening rate
Greater than or equal to 80% of eligible participants will agree to enrol
Greater than 80% of participants in the intervention groups will receive their allocated treatment (measured twice weekly whilst participant recruited to study)
Less than 10% of data collection for primary outcomes will be missing
Less than or equal to 40% of participants will be lost to follow-up, withdraw from the study or be deemed ineligible after they have commenced treatment

### Intervention primary outcomes

Questionnaires will be administered to obtain qualitative and quantitative data regarding the feasibility, appropriateness and acceptability of staff, parents and participants using NPWT in acute paediatric hand and foot burns.

#### Staff questionnaire

A mixed method questionnaire incorporating Likert scales and open-ended questions will be developed using Weiner and colleagues’ model for implementation studies [34]. The three criteria addressed are acceptability (is it ethically justifiable to use NPWT in paediatric hand and foot burns), appropriateness (the impact of NPWT on wound re-epithelialisation) and feasibility (is it physically possible to implement NPWT). This questionnaire will be asked at the start and end of the trial to see if the perception of NPWT has changed over the study period. In addition, feasibility of both current standard dressings vs NPWT will be asked in a combined Likert scale and open-ended questionnaire at the point of the first dressing change to assess patient-level data.

#### Participant questionnaire

A mixed method questionnaire incorporating Likert scales and open-ended questions will be administered assessing feasibility at the first dressing change. The questions will address the ease/difficulty and confidence of performing, maintaining and adhering to the assigned dressing. This will allow an analysis of whether there is any perceived difference amongst patients between the dressings.

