NPWT is a device that optimises wound healing through various mechanisms including establishing a tissue pressure gradient [23], enhancing the wound bed environment, [24] micro- and macro deformations, encouraging cell mitosis [25] and promoting angiogenesis and lymphangiogenesis [26]. Our study team, led by [name] et al., completed a single-site randomised control trial (RCT) of 114 Australian children aged up to 16 years with small, superficial partial thickness paediatric burns and found that NWPT applied within the first 7 days, compared to standard dressings of Mepitel® and ACTICOAT™, decreased the time to re-epithelialisation by 22% (95% CI 7 to 34%) [27]. Through a sub-analysis, it was also identified that when NPWT was applied within the first 24 h, this group re-epithelialised faster than those who had late application [27]. We believe the benefit of NPWT is in modifying the initial progression of the zone of stasis and thus the benefit of NPWT is within the first 72 h. This is also supported by early porcine work in the 1990s [28]. We have therefore altered the application time from our first trial to application occurring within the first 24 h rather than 7 days and removed at the first dressing change—at least 72 h after application without re-application as opposed to when the burn is completely re-epithelialised. However, this study also found that the use of NPWT on paediatric patients had associated burden including the bulk of the device, mechanical issues and difficulties with school attendance. Furthermore, using NPWT on hand and foot burns was often considered inappropriate due to the perceived difficulty of application [27]. Despite this burden, clinicians believe that the burden of NPWT in paediatric hand and foot burns is outweighed by the advantage of decreasing the likelihood of hypertrophic scar formation. We have designed a pilot study to address the specific concerns from the trial by [name] and colleagues, including that hand and foot burns are not a feasible place to apply NPWT and the extent of the burden of the device.

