### Recruitment/consent

Burns Team and/or Emergency Department (ED) staff will notify researchers of eligible participants presenting to either the ED or the PLCBC. An investigator will provide the patient/family with information (both verbal and written) on the trial, and if the patient/family agrees, they will be asked to sign a consent. Where the participant does not speak English as their first language, an interpreter will be offered. A third party will be present throughout to ensure no coercion and will also sign the consent. If the family does not agree, they will be asked to consent to their baseline demographic data being included. When consenting, it is ensured that the participants/families know they have the autonomy to withdraw from the study at any stage.

Throughout the participants’ treatment, researchers will be independent of any clinical decision making processes regarding the participants. Treating clinicians will decide where the debridement occurs (i.e. theatre, ED, PLCBC) and whether it is appropriate for the patient to be enrolled in the study. Demographic data (i.e. burn details, medical, surgical and social history) will be collected before randomisation into the study.

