#### Intervention

Participants will include application of the RENASYS TOUCH™ device (Smith & Nephew, Hull, UK) in addition to standard dressings. Kerlix™ AMD Antimicrobial bandage roll (CardinalHealth, Dublin, USA) is first placed as an interface between the standard dressings and NPWT device, then a Suprasorb® CNP EasyDress sleeve (Lohmann & Rauscher, Rengsdorf, Germany) applied over the standard dressing + Kerlix™ and secured with the provided film (± additional semi-permeable transparent film dressing as required to achieve seal). A small hole (< 30 mm) will be cut in the Suprasorb® CNP EasyDress sleeve over the site of the burn and a soft port applied over the hole, ensuring the hole in the EasyDress aligns with the hole of the soft port. The soft port is then attached to a cannister which is attached to the RENASYS TOUCH™ NPWT device. Suction will be applied continuously at either 80 mmHg for children > 1 years old, 60 mmHg for 6 months–1 year or 40 mmHg < 6 months old. If bilateral hands and/or feet are involved, the deeper one will have NPWT applied. If both are assessed to be of equal depth, then NPWT with a y connector will be used. The NPWT will remain on for the first 3–7 days and then removed at the first dressing change; it will not be reapplied after this. Once the NPWT is removed, treatment will continue as per the control group with standard dressings.

Throughout the trial, strategies to improve NPWT adherence will include a backpack to carry the device, dressing packs on discharge that include extra tape to help seal any leaks, education (both written and verbal) on the device and where to call to help trouble shoot issues on discharge.

Criteria for discontinuing or modifying allocated interventions for a given trial participant will include the following: on debridement of the burn, it no longer meets the eligibility criteria (i.e. burn is actually only SPT and is < 0.5% TBSA) or there is an adverse outcome requiring at least admission to the paediatric intensive care unit (PICU). Patients who become septic but are not admitted to PICU or require grafting will remain in the study.

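### The only stated family questionnaire comes at the first dressing change, so families who leave the study before that visit are not asked and the NPWT ratings could be biased upwards

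*Protocol article*

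**What the plan says.** Under Intervention primary outcomes, the article says that questionnaires will supply "qualitative and quantitative data regarding the feasibility, appropriateness and acceptability of staff, parents and participants using NPWT". This makes family views part of a primary outcome.

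For families, the section Participant questionnaire gives one time point: the instrument "will be administered assessing feasibility at the first dressing change". Its content is described thus: "The questions will address the ease/difficulty and confidence of performing, maintaining and adhering to the assigned dressing". The same section intends a comparison of perceived difference between the two dressings.

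The patient-level staff form in Staff questionnaire depends on the same visit; it is asked "at the point of the first dressing change to assess patient-level data".

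Under Intervention, "The NPWT will remain on for the first 3–7 days and then removed at the first dressing change". Under Recruitment/consent, families are told that "they have the autonomy to withdraw from the study at any stage". The Introduction reports from the team's previous trial "associated burden including the bulk of the device, mechanical issues and difficulties with school attendance".

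The article describes no questionnaire for a family that leaves before the first dressing change.

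**The concern.** The family measurement depends on attending a visit, and only families still in the study attend it. The device is worn entirely before that visit, so any withdrawal prompted by wearing it happens before the family is asked. Control families have no device to withdraw over, so loss of this kind would fall on the NPWT arm alone.

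The families who found the device hardest to live with may therefore be the ones whose answers are missing. The Discussion describes the trial as chiefly a study of barriers to NPWT, so these would be among its most informative respondents. Both the NPWT ratings and the comparison between dressings could be shifted towards NPWT. An intention-to-treat analysis, preferred under Data analysis, does not repair this, because it cannot recover an answer that was never collected.

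**Working it through.** **Inputs from the article**
- NPWT arm: about 15 of 30 children (Trial design, Sample size).
- Device worn for 3–7 days, ending at the first dressing change (Intervention).
- Family questionnaire: first dressing change only (Participant questionnaire).
- Limits in Table 2: more than 80% of the intervention group receive allocated treatment; less than 10% of primary outcome data missing; at most 40% lost, withdrawn or ineligible.

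**Assumptions, because the article gives no figure**
- m = number of NPWT families who leave before the first dressing change.
- f = share of NPWT respondents with a favourable view. The article describes Likert and open-ended items and no favourable/unfavourable split, so f is a device for showing size. The main case uses f = 83.3% (10/12).
- Worst case: every family that leaves would have been unfavourable.

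**1. The plan's own precision figure.** The article gives no expected value for the questionnaire. The nearest figure is the margin for treatment received in the NPWT arm, ±18% at 87%. It reproduces as 1.96 × √(0.87 × 0.13 / 14) = 17.6%, which rounds to 18%. It concerns a different quantity and serves here only as a scale.

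**2. Size of the possible bias.** Share favourable over all randomised to NPWT = f × (15 − m)/15. Overstatement = f × m/15.

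| m | f × (15 − m)/15 at f = 83.3% | Overstatement | Overstatement at f = 70% to 90% |
|---|---|---|---|
| 0 | 83.3% | 0 | 0 |
| 1 | 0.833 × 14/15 = 77.8% | 5.6 points | 4.7 to 6.0 points |
| 2 | 0.833 × 13/15 = 72.2% | 11.1 points | 9.3 to 12.0 points |

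**3. Would Table 2 flag it?** Count one family questionnaire per child, and treat an early leaver as not having received treatment.
- m = 1: missing 1/30 = 3.3%; treatment received 14/15 = 93.3%. Both pass.
- m = 2: missing 2/30 = 6.7%; treatment received 13/15 = 86.7%. Both pass. Counted within the NPWT arm, 2/15 = 13.3% fails the missing-data limit. Table 2 does not say which denominator applies.
- m = 3: missing 3/30 = 10.0%, which is not below 10%; treatment received 12/15 = 80.0%, which is not above 80%. Both fail.

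The 40% limit does not bind at any of these values. The range that could pass unnoticed is therefore 1 or 2 families.

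**4. How likely are two or more losses?** If each NPWT family has probability q of leaving before the first dressing change, P(m ≥ 2) = 1 − (1 − q)^15 − 15q(1 − q)^14. For assumed q of 5%, 10% and 20% this is 17%, 45% and 83%.

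**The case against.** The strongest reply is that the mechanism is narrow. The questionnaire is tied to an event, not a calendar day, and both arms need that event for burn care. A family that only wants the device off has not left the study. If staff remove it early with a dressing change, that visit can itself be the first dressing change. This stands: the gap concerns families who withdraw consent or do not return, and some of them would decline an exit questionnaire too.

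A reader might infer that early leavers disappear from the primary outcomes or appear only in a pooled attrition count. The article does not support that. They also count in the missing-data criterion and can count against treatment received, which is specific to the NPWT arm and checked twice weekly. Safety/harm also grades deviations from the intervention and takes parent reports. What these measures are not described as capturing is the family's view, or device burden as the reason for leaving.

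Other points also stand. The only place where the article anticipates higher dropout is the 3-month follow-up. The burdens in the Introduction come from a trial in which NPWT stayed on until re-epithelialisation, so they may be milder here. Participant questionnaire speaks of feasibility, and family acceptability rests on the general statement under Intervention primary outcomes. The shift for 1 or 2 families lies within the ±18% that the plan accepts for another proportion in this arm. Finally, the article condenses a fuller protocol, and an exit form or a field for withdrawal reasons may exist there. The point therefore rests on the timing that the article states, not on the absence of such a form.

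**Conclusion.** The concern holds in a conditional form. The one stated family measurement follows all device wear and reaches only families still in the study, so its results could be biased in favour of NPWT. A reader might go further and conclude that NPWT will look more acceptable than it is. The documents do not support that: they give no rate of withdrawal before the first dressing change, and with none the bias is zero.

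For losses that can pass the Table 2 limits (1 or 2 of 15, with missing data counted over all 30), the overstatement is about 6 to 11 points. This rests on an assumed 83% favourable among respondents and on every lost family being unfavourable. Larger losses would be visible, since three of 15 fail both the missing-data and the treatment-received limits. This is a worthwhile, inexpensive improvement to a primary outcome and does not undermine the trial.

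**What to change.** - Give the existing family questionnaire at the first dressing change or at study withdrawal, whichever comes first, and only with the family's agreement. REDCap is already in use for the questionnaires, so this adds a trigger and no new instrument.
- Record one main reason for early NPWT cessation or study withdrawal (for example device burden, device fault, clinical, other) and report these by arm.
- Keep the respondent result. Beside it, give a sensitivity result over all children randomised to NPWT that counts withdrawal for device burden as unfavourable.

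The cost is one extra trigger, one field and one line in the results. Some withdrawing families will decline to answer, and the reported figure may be lower. If the full protocol already has such a form, it is enough to say so and add the sensitivity result.

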#### Safety/harm

Safety/harm will be classified based on the number and severity of adverse outcomes. The adverse outcome will be graded based on a modified Clavien-Dindo scale [35]. This is an objective way to quantify the severity of an event from grade one, a deviation from intervention, to grade five, death.

Adverse events will be recorded in an ‘Adverse Outcome Logbook’, stored in a locked cabinet at the Centre for Children’s Health Research. A grade will be given for each day the adverse event occurs. Parents of the participants will be provided with contact details for the burns centre to report any adverse events that may occur during the study. In addition to self-report, parents/participants will be questioned at each clinic appointment through the duration of wound care.

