**Methods and analysis:**

This is a single-site, pilot randomised control trial. Participants must be aged ≤ 16 years, otherwise well and managed within 24 h of sustaining either a hand or foot burn. Thirty participants will be randomised to either standard care (Mepitel®—a silicone wound interface contact dressing—and ACTICOAT™—a nanocrystalline silver-impregnated dressing) or standard care plus NPWT. Patients will be reviewed until 3 months post-burn wound re-epithelialisation, with measurements taken at dressing changes to assess primary and secondary outcomes. Surveys, randomisation and data storage will be done via online platforms and physical data storage collated at the Centre for Children’s Health Research, Brisbane, Australia. Analysis will be performed using the Stata statistical software.

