## Methods/design

### Hypothesis and objectives

It is hypothesised that NPWT is feasible, acceptable and safe in paediatric hand and foot burns. Furthermore, it is also hypothesised that by utilising NPWT, burns will have a decreased time to re-epithelialisation and reduced pain, itch, infection and scar formation.

The primary objectives of this pilot study are to determine the feasibility, acceptability and safety of the use of NPWT in paediatric hand and foot burns. The secondary objectives will include investigating time to re-epithelialisation, pain, itch and scar formation. If further research is required, this pilot will help guide the methodology of a larger RCT. Ultimately, this study may inform the integration of NPWT into routine, acute paediatric burns care.

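### Active adverse-event questioning ends at healing, which NPWT is expected to bring forward, so raw event counts are not a like-for-like safety comparison

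*Protocol article*

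**What the plan says.** The protocol article makes safety a primary aim (Hypothesis and objectives): "The primary objectives of this pilot study are to determine the feasibility, acceptability and safety of the use of NPWT". The measure is given under Safety/harm: "Safety/harm will be classified based on the number and severity of adverse outcomes". The same section adds: "A grade will be given for each day the adverse event occurs".

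Events are found by two routes, both under Safety/harm:

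- **Self-report.** "Parents of the participants will be provided with contact details for the burns centre to report any adverse events that may occur during the study".
- **Active questioning.** In addition, "parents/participants will be questioned at each clinic appointment through the duration of wound care".

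Four other sections determine how long active questioning lasts and how counts are compared:

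- **Control (under Intervention):** dressings are changed every 3 to 7 days until the treating clinician judges the burn re-epithelialised. After the device is removed, the NPWT arm follows the same course.
- **Blinding:** treating clinicians know the allocation. The blinded photograph panel sets the healing outcome, not the end of wound care.
- **Hypothesis and objectives:** NPWT is expected to shorten time to re-epithelialisation.
- **Data analysis:** counts are compared by Poisson regression, with estimates and 95% confidence intervals and no formal testing.

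Follow-up is longer than active questioning. The abstract states: "Patients will be reviewed until 3 months post-burn wound re-epithelialisation". The section on the 3-month scar and skin assessment plans a face-to-face visit for all participants and mentions no adverse-event question.

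**The concern.** The period in which families are actively asked about harm closes at an event that the treatment is expected to bring forward. The closing point is also set by someone who knows the allocation. If NPWT works as hypothesised, children in that arm are asked over a shorter time and possibly at fewer visits. After healing, the stated route for adverse events is self-report, so the intensity of ascertainment changes at a different time in each arm.

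Safety is judged on counts, and each day of an event receives a grade, so a day-based tally also grows with the days observed. A lower total in the NPWT arm could therefore partly reflect less asking. An analysis plan could add an exposure term or split the table by period, but it could not recover events that nobody asked about. For that reason the point concerns data collection and not only analysis.

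**Working it through.** The article gives no expected adverse-event figure or precision for safety, so there is no stated number to reproduce. The check asks how far unequal questioning could move a count ratio.

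**Inputs from the protocol article**
- Reduction in healing time, r: 22% (95% CI 7 to 34%), from the earlier trial described in the Introduction.
- Visit interval: 3 to 7 days (Control).
- Time on NPWT: the first 3 to 7 days, not reapplied (Intervention).
- About 15 children per arm (Trial design).

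**Assumptions, not in the documents**
- Control healing time T = 14 days.
- Share of control-arm events in the first 5 days: 75%.
- One event per control child.

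**Step 1: constant event rate, events found only by questioning.** Expected counts per child are rate × T in control and rate × T × (1 − r) with NPWT. With equal rates the count ratio is 1 − r:
- r = 0.22: 0.78
- r = 0.07: 0.93
- r = 0.34: 0.66

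Conversely, a count ratio of 1 would correspond to a rate ratio of 1/0.78 = 1.28 (1/0.93 = 1.08 to 1/0.66 = 1.52). The whole of this is artefact only if events continue at the same rate after healing and go unrecorded.

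**Step 2: events clustered early.** Let a share f of control-arm events fall in the first 5 days, seen equally in both arms, with the rest spread evenly to healing. The ratio is f + (1 − f) × [T(1 − r) − 5]/(T − 5). With f = 0.75 and T = 14:
- r = 0.22: 0.75 + 0.25 × (10.92 − 5)/9 = 0.91
- r = 0.07: 0.75 + 0.25 × (13.02 − 5)/9 = 0.97
- r = 0.34: 0.75 + 0.25 × (9.24 − 5)/9 = 0.87

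**Step 3: number of times the question is asked.** Visits are healing time divided by the interval, rounded up. With T = 14 and r = 0.22, NPWT healing takes 14 × 0.78 = 10.9 days.
- Visits every 3 days: 5 in control, 4 with NPWT.
- Visits every 7 days: 2 in control, 2 with NPWT, so no difference.

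**Step 4: sampling error.** With 15 expected control events and 15 × 0.78 = 11.7 NPWT events, the standard error of the log ratio is √(1/15 + 1/11.7) = 0.39. The 95% interval around 0.78 is 0.78 × exp(±1.96 × 0.39), or about 0.36 to 1.68. Chance variation is wider than the possible distortion.

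**The case against.** The case against giving this much weight is substantial, and most of it stands as a limit on size.

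- **Device harm falls in a shared period.** The device comes off at the first dressing change, and controls have theirs on the same 3 to 7 day schedule. Harm while the device is worn is therefore sought alike in both arms.
- **Self-report continues in both arms.** Admissions and operations are also recorded for the cost analysis, and the 3-month review covers pain, tightness and range of motion. Late harm is not unobserved, though none of these is the same adverse-event question.
- **Fewer wound events may be real benefit.** If complications need an open wound, earlier closure prevents them, and a fixed observation window would show much the same reduction.
- **The 22% is borrowed.** In the earlier trial NPWT could start within 7 days and continued until healing, in small superficial partial thickness burns. Here it starts within 24 h, stops at the first dressing change, and deep burns are eligible.
- **Other features could act in the opposite direction.** Grade one covers departures from the intervention, and NPWT families are told where to call about device problems. Both could raise recorded events in the NPWT arm.

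A reader might infer that the safety comparison is biased towards NPWT by about 22%, or that the trial will call NPWT safe because of a shorter look. The documents support neither. The first needs a constant event rate persisting after healing, no self-report and an effect transferred from another regimen, and the net direction is not established. As to the second, the feasibility criteria in Table 2 contain no safety threshold, and no formal testing is planned.

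What remains is that active ascertainment for a primary objective stops at a point that depends on treatment, and total counts over that window mix unequal observation with real effect.

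**Conclusion.** The concern holds in a limited form. Active questioning ends at clinician-judged healing, which NPWT is expected to shorten, so raw counts over that window are not a like-for-like comparison, and events after healing depend mainly on self-report.

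The possible distortion runs from about 0.78 (0.93 to 0.66), under the least favourable assumptions and a borrowed healing effect, through about 0.91 (0.97 to 0.87) with early clustering, to negligible with 7-day visits. Event rate, event timing and control healing time are assumptions. Part of any reduction would be genuine, and the overall direction of bias is not known. With about 15 children per arm, sampling error is larger than any of these figures.

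This is a cheap improvement to data collection and reporting. It does not invalidate the pilot's safety objective, but it is worth making because the results are meant to guide a larger trial that could inherit the same window.

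**What to change.** 1. At the 3-month visit already scheduled, ask the same adverse-event question in both arms, covering the time since wound care ended.
2. Report events from application of the allocated dressing to the first dressing change, in both arms, as the main device-safety comparison.
3. Show later events in a separate table, with events per day observed alongside the raw counts.

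The 3-month visit is itself timed from healing, so total observation would still differ between arms, but by much less. Under the assumed 14-day control healing and a 22% reduction, and taking 3 months as 90 days, the ratio of total time is (10.9 + 90)/(14 + 90) = 0.97 in place of 0.78.

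The cost is one question and one table. The event count may rise slightly, and recall of late events will be imperfect. Children who miss the visit stay unasked. The article expects more dropout at 3 months when there is no scar, and Table 2 tolerates up to 40% of participants lost, withdrawn or found ineligible, so the number asked in each arm should be reported. No change to treatment, eligibility or sample size is needed.
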